### Neuropsychological assessment

A neuropsychological assessment is administered at each stage of the study using the Italian version of the NEPSY-II battery. The NEPSY-II is designed to evaluate six different cognitive domains in children and adolescents aged 3–16 years. In our study, we administer tests that assess visual attention and executive functions, visuospatial memory and functions, sensorimotor integration and social perception skills. The Visual Attention test assesses speed and accuracy of patients in focussing and maintaining attention on visual targets among a series of distracting stimuli. To assess executive functions, we adopt the Inhibition test, in which participants are asked to denominate different figures respecting diverse rules, thus inhibiting automatic responses. In the Memory for Drawing test, children are exposed for 10 s to a table representing drawings in diverse spatial positions and then they are asked to choose the correct stimuli in a series of cards and place them in a panel in the same position that they have seen before. The recall is asked immediately after the exposition and after 20 min. The Picture and the Geometric puzzles use, respectively, concrete and abstract examples to evaluate visual-perceptual and visual-spatial representation abilities. For sensorimotor integration, we administer the Finger-tapping test, which measures the ability to repeat fast finger movements and maintain a motor programme. To assess social perception skills, we administer the Theory of Mind and the Affect Recognition tests. The first is composed of two parts resulting in one score. In the verbal part, verbal or pictorial descriptions of social situations are presented in order to evaluate the ability to understand mental constructs, such as beliefs and intentions, and how other people could have thoughts, emotions and perspectives, which might be different from ours. Conversely, the contextual part assesses the ability to infer others’ emotional and mental states by social context. The Affect Recognition test provides a measure of the ability to recognise affective states from emotional facial expressions using pictures of children. Moreover, the baseline assessment includes a full cognitive evaluation with the Wechsler Intelligence Scale for Children, 4th edition (WISC-IV) to estimate IQ scores [57].

### Questionnaires

At the baseline (T0) and follow-up evaluations (T3) the TACQOL is administered to parents and children. This questionnaire has been primarily designed for research and evaluates quality of life in diverse domains: body, movements, autonomy, cognitive abilities, sociality and positive and negative emotionality. At the same time points, parents are asked to compile the CBCL, the most adopted questionnaire regarding the behaviour of children and adolescents. This questionnaire provides scores for eight empirically based syndrome scales, namely aggressive behaviour, anxiety/depressive symptoms, attention problems, rule-breaking behaviour, somatic complaints, social problems, thought problems and degree of withdrawal. These scales are further aggregated in three main dimensions: internalising, externalising and total problems.

### Statistical methods

Demographic, clinical and neuropsychological variables of the two groups of patients are inspected through descriptive statistics. A *t* test and *χ*^2^ are used to assess the differences between the experimental and control training groups at baseline for continuous and categorical variables, respectively, thus allowing us to verify successful randomisation. For each outcome measure, we calculate the change between T0 and T2 (training effect delta) and between T0 and T3 (follow-up effect). Delta is calculated as the arithmetic difference between the second/third time points and the first time point. The delta values of the two groups for the primary outcome measure are compared using independent sample *t* tests (two-tailed). For the primary outcome measure, a Bonferroni correction procedure will be used to control for multiple comparisons. Multivariate analysis of variance will be used to explore differential effects of the trainings in the secondary outcome measures. As to what concerns missing data, a modified intention-to-treat analysis approach will be adopted, including in the analyses all the participants who had completed the pre- and post-treatment evaluation sessions, even if they had not completed all the training sessions. No imputation of missing data, however, will be used considering the limited sample size and observation points [58, 59]. The stratification factors (i.e. age and FSIQ), will not be considered in the statistical analyses, assuming that the stratification procedure has ensured a balanced distribution across the two groups.

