### Design

The study applies a single-centre, randomised, active-controlled trial design. Patients are allocated to one of two groups undergoing two different rehabilitation programmes through a stratified permuted block randomisation procedure [47]. Age and cognitive level (more recently available Full-scale Intelligent Quotient, FSIQ) are chosen as stratification factors. In particular, we consider two levels for age, corresponding to 7.0–12.9 and ≥ 13.0 years, and three stages for cognitive level consistent with, respectively, absence of intellectual disability (FSIQ > 80), from borderline intellectual functioning to mild intellectual disability (80 ≥ FSIQ ≥ 61) and from mild to moderate intellectual disability (60 ≥ FSIQ ≥ 45) (48). Doing so, six blocks are generated and within each block an estimated number of eight patients should be enrolled to achieve and overcome the established sample size. First, participants are allocated to a block depending on the two stratification variables. Second, patients are assigned to one of the two interventions according to specific permuted sequence. Details of the permuted blocks are reported in Table 1.

**Table 1 Tab1:** Stratified permuted blocks randomisation of the study

		Age	
		7–12.9 years	≥ 13.0 years
FSIQ	46–60	CCSSCCSS	SCSCSCSC
	61–80	SCCSSCCS	SSCCSSCC
	> 80	CSCSCSCS	CSSCCSSC

Legend: *FSIQ* Full-Scale Intelligent Quotient, *S* VR-Spirit training, *C* control training

Group 1 (S) receives the social prediction VR training for 2 weeks (four daily sessions in a week). In each 1-h session, 80 trials of the experimental programme and one of four motor games, selected among the applications available in the GRAIL, are administered; for each weekly session, a different game is administered in random order. Group 2 (C) receives a control VR training of the same duration (2 weeks, four 1-h sessions per week) as the experimental training; the control training involves, for each session, a navigational game and the daily repetition of all the four games from the GRAIL suite that are also presented, one per day, in the experimental session; the social prediction experimental programme is not presented in the control training.

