Before the training (T0), a battery of neurocognitive tests from the Developmental NEuroPSYchological Assessment, 2nd edition (NEPSY-II [49, 50];) spanning different domains, and, specifically, social perception abilities, is administered to all participants. Both groups also receive a 10-min training of how to move within the GRAIL environment using a custom-made navigational application. Then, a pre-training evaluation through a VR game session, based on the same paradigm of the VR experimental training but in a different scenario, and a computer-based Action Prediction task [51] are administered. Moreover, at T0, both patients and parents compile questionnaires on quality of life (Tno-Azl (Netherlands Organisation for Applied Scientific Research Academic Medical Centre) Children’s Quality Of Life questionnaire (TACQOL), TNO Quality of life/LUMC, 2001 [52];) and parents also complete the Child Behaviour Check List (CBCL [53, 54];).

Performance at the VR tasks is monitored for all the sessions of the training period (T1). In order to verify and compare the effects of the experimental and control training sessions, at the end of the 2-week training (T2) all participants are re-evaluated with the same neurocognitive tests, the VR evaluation scenario and the Action Prediction task.

With the aim to investigate the far transferability of the effects, a follow-up evaluation is provided after 2 months (T3) with the same protocol used at T0 except for the GRAIL evaluation scenario. Details of the study design are set out in Fig. 1 according to the Standard Protocol Items: Recommendations for Interventional Trials (SPIRIT) Statement [55, 56] (see also Additional file 1).

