### Outcome measures

Primary outcome measure:
Social prediction ability: performance during the pre- (T0) and post-training (T2) evaluation in the sweet stands’ scenario; standardised beta-coefficients of the regression between accuracy and probability in the testing phase of the validated PC-based Action Prediction task administered before/after the intervention (T0, T2) and at the follow-up visit (T3)

Secondary outcome measures:
Social cognition: Theory of Mind Parts A and B and Emotion Recognition of the NEPSY-II testing batteryImplicit learning: accuracy and reaction time in the familiarisation phase of an Action Prediction taskExecutive functions (inhibition and flexibility): Inhibition test of NEPSY-IIVisual attention: Visual Attention test of NEPSY-IIVisuospatial and visual-perceptual abilities: Geometric Puzzle and Picture Puzzle tests of NEPSY-IIMemory: Memory for Drawings test of NEPSY-IISensorimotor functions: Finger-tapping of NEPSY-IIBehavioural problems: CBCL 6–18, Parent versionOverall functioning and quality of life assessed using the TACQOL questionnaire, presented in two forms: the self-compiled one and the parent-compiled one

To assess training feasibility:
Number of dropouts: number of children who renounce to complete the 2-week trainingNumber of sessions completed per child: total number of sessions performed in front of the total number proposed of eight sessions

To assess training acceptability:
Acceptability questionnaire: an ad-hoc questionnaire completed by participants and another one by their parents after training conclusion (T2) to assess subjective evaluation of training accessibility and efficacy. It is to note that the same questionnaires are fulfilled by the patients of the active control group and their parents

A psychologist, who is not blinded to the intervention assignment, administers all the neuropsychological tests and questionnaires and records the performance during the GRAIL sessions.

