### Estimation of sample size

Estimation of sample size was based on the distribution of the standardized beta-coefficients of the regression between accuracy and probability in the PC-based, contextualised Action Prediction task in children with typical development (M = 0.154, SD = 0.215) and with ASD (M = 0.008, SD = 0.112), with a between-group difference of moderate-to-large size (Cohen’s *d* = 0.87; see Amoruso et al., 2019 [45]). Given the difference in the standardised beta-coefficient between children with typical development and with ASD, an increase of moderate effect size in this outcome measure should represent a clinically relevant improvement in the ability to form predictive models of others’ behaviour, with a likely impact on social deficits and autism-like behaviours shown by patients with cerebellar malformations. Thus, we estimated that a moderate increase (0.13 mean change or 0.8 SD) of the standardised beta-coefficient after as compared to before the experimental training had clinical significance. Accordingly, a final sample of 21 patients per group has been set for our study in order to detect a between-group difference (independent sample *t t*est, two-tailed) between the effects of the experimental vs*.* control training (T2 − T0) of moderate effect size (Cohen’s *d* = 0.8) with a power of 0.80 and an alpha level set at 0.05. The software G Power 3 was used for this estimation.

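### The primary outcome implies two or three Bonferroni-corrected tests, but the sample size covers one at unadjusted alpha 0.05, and one of the measures uses the trained paradigm

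*Protocol article*

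**What the plan says.** Under Outcome measures, one primary outcome (social prediction ability) is defined through two instruments. The first is "performance during the pre- (T0) and post-training (T2) evaluation in the sweet stands" scenario. The second is the standardised beta from the testing phase of the computer-based Action Prediction task, measured at T0, T2 and T3. The Design section says that T3 is run "with the same protocol used at T0 except for the GRAIL evaluation scenario", so the VR measure has no follow-up contrast.

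Statistical methods computes T2−T0 and T3−T0 changes for each outcome and compares the primary changes between groups with two-tailed independent-sample t tests. It adds: "For the primary outcome measure, a Bonferroni correction procedure will be used to control for multiple comparisons". The number of comparisons is not given.

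Estimation of sample size sets 21 patients per group to detect d = 0.8 on the T2−T0 change, with the effect derived from the Action Prediction beta alone, "with a power of 0.80 and an alpha level set at 0.05".

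On the VR measure, the Design section describes the evaluation as "based on the same paradigm of the VR experimental training but in a different scenario". For the control arm it says that "the social prediction experimental programme is not presented in the control training".

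**The concern.** The analysis section divides alpha across several primary tests, while the sample size spends the whole 0.05 on one. If the correction is applied as written, each primary test has less power than the protocol claims, including the contrast on which the trial was sized. In a trial of 42 patients this could turn a real effect of the size called clinically significant into a null result.

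The second issue is what a positive result would mean. With two instruments listed together and a Bonferroni rule, a significant VR score could support the primary claim by itself. Only the experimental arm trains on that paradigm, so the VR score alone cannot fully separate better social prediction from familiarity with the game format. The Action Prediction task is trained in neither arm and does not have this difficulty.

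**Working it through.** **Inputs.** 21 per group, d = 0.8, two-tailed independent-sample t test, alpha 0.05, power 0.80 (Estimation of sample size). Bonferroni for the primary outcome, with T2−T0 and T3−T0 changes (Statistical methods). Two instruments (Outcome measures). No VR evaluation at T3 (Design).

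**Step 1: count the primary tests.**

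| Measure | T2−T0 | T3−T0 |
|---|---|---|
| VR evaluation performance | yes | not measured |
| Action Prediction beta | yes | yes |

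This gives three tests, or two if the follow-up effect is kept outside the correction. The count could be higher: the Evaluation sessions section lists several recorded VR variables (trial duration, speeds, victory, score), and the outcome definition does not say which one is performance.

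**Step 2: reproduce the plan's own figure.** Power = P(|T| > t_crit), where T is noncentral t with df = 2n − 2 and noncentrality d × √(n/2). At n = 21, df = 40 and the noncentrality is 0.8 × √10.5 = 2.592.

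- Two-sided 0.05: t_crit = 2.021, power 0.716. Power is 0.791 at n = 25 and 0.807 at n = 26, so 26 per group are needed.
- One-sided 0.05: t_crit = 1.684, power 0.817 at n = 21 and 0.799 at n = 20, so 21 per group are needed.

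The stated 21 does not reproduce for the stated two-tailed test. It is the answer for a one-tailed test.

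**Step 3: apply the planned correction** (d = 0.8 assumed for every contrast).

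| Tests | Alpha per test | t_crit (df 40) | Power per test, 21 per group | n per group for 0.80 | Smallest d with 0.80 power at 21 per group |
|---|---|---|---|---|---|
| 1 | 0.05 | 2.021 | 0.716 | 26 | 0.89 |
| 2 | 0.05/2 = 0.025 | 2.329 | 0.606 | 31 | 0.98 |
| 3 | 0.05/3 = 0.0167 | 2.499 | 0.542 | 35 | 1.04 |

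**Step 4: split the shortfall.** From 0.80 to 0.716 is the sizing discrepancy (0.084) and has nothing to do with multiplicity. From 0.716 the correction costs a further 0.716 − 0.606 = 0.110 for two tests, or 0.716 − 0.542 = 0.174 for three. None of these figures allows for dropout. The article states no inflation and rules out imputation.

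**Step 5: exposure to the VR paradigm before the T2 evaluation.** Experimental arm: 8 sessions × 80 trials = 640 in training, plus 80 at the T0 evaluation = 720. Control arm: 0 in training, plus 80 at T0 = 80.

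**The case against.** Several points on the other side have force.

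- **Bonferroni is conservative.** A reader might infer that the primary analysis inflates false positives. It does not: the planned correction protects type I error, and the multiplicity defect concerns power only. Nor is correcting at analysis after sizing at 0.05 logically impossible; it simply leaves the trial underpowered against its own statement.
- **The divisor of three is an inference.** The article names the T3 change separately as a follow-up effect, so correcting over the two T2 contrasts alone is a possible reading. The result then is 0.61 rather than 0.54, still short of 0.80.
- **Power per test is not the power of the trial.** It would be wrong to say that the trial as a whole has 54% power. If any one significant test counts, with three tests and d = 0.8 throughout, the chance of at least one success runs from 0.54 (perfectly correlated tests) to 1 − (1 − 0.542)³ = 0.90 (independent tests). But the sample size statement is about one named contrast, and for that contrast the power per test is the relevant figure.
- **The VR evaluation is not the trained task itself.** A reader might infer that it is, or that controls never meet the paradigm. The documents support neither. The setting and objects differ, the avatar-object associations change between sessions, and two evaluation versions are used in counterbalanced order, so learned preferences should not carry over. Both arms play 80 evaluation trials at T0, both receive navigation training, and controls play a navigational game at every session. What can carry over is familiarity with the format and skill in forming new associations, and the latter is the ability being targeted. The practice concern therefore stands only as partial confounding by format practice or near transfer.

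**Conclusion.** The sample size does not deliver the stated 80% power under the planned analysis. At 21 per group and d = 0.8, power per test is 0.61 with two corrected tests and 0.54 with three. Blaming the whole gap on Bonferroni would be wrong: uncorrected power is already 0.716, because 21 per group fits a one-tailed test and the two-tailed test needs 26.

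These figures rest on the inferred number of tests and on d = 0.8 for each contrast. The article gives that effect only for the beta at T2−T0; it gives none for VR performance or for T3.

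The shared paradigm is a lesser, interpretive point: a gain on the VR score may partly reflect practice, by an amount the documents do not allow one to estimate. It matters because nothing in the article stops that score from carrying the primary claim alone.

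**What to change.** **Preferred.** Name the Action Prediction testing-phase beta, T2−T0, as the single primary endpoint at two-sided alpha 0.05; this is the contrast already used for sizing. Move the VR evaluation (labelled as near transfer) and the T3 beta to the secondary outcomes, and remove the Bonferroni sentence for the primary outcome. This makes alpha consistent but does not restore 80% power. Restate power at 21 per group as about 72% for d = 0.8, with 80% reached only for d of about 0.89.

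**Alternative.** Keep the co-primaries, state the Bonferroni divisor and which contrasts it covers, and restate power per test as 0.61 (two tests) or 0.54 (three tests).

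**Cost.** Changes to the protocol and registry wording. Under the preferred option the VR score no longer carries the primary claim; under either option the stated power is less favourable. Trial status shows that recruitment is under way, and the article says that the assessing psychologist is not blinded. Demoting a listed primary measure and dropping a conservative correction could therefore draw criticism of their own. The change should be a dated amendment that records that it was made without reference to outcome data.

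### Holm's step-down procedure would be a cheap, optional improvement on the planned Bonferroni correction of the primary tests, but it gains power only if more than one primary effect is real

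*Protocol article*

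**What the plan says.** All references are to the protocol article.

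- **Outcome measures** places two measures under one primary outcome, social prediction ability. The first is "performance during the pre- (T0) and post-training (T2) evaluation" in the sweet stands' scenario. The second is the standardised beta-coefficient of the Action Prediction task, "administered before/after the intervention (T0, T2) and at the follow-up visit (T3").
- **Design** says that follow-up is done "with the same protocol used at T0 except for the GRAIL evaluation scenario", so the VR measure has no T3 value.
- **Statistical methods** calculates T2−T0 and T3−T0 changes for each outcome, compares the arms on the primary changes with two-tailed independent-sample t tests, and adds: "For the primary outcome measure, a Bonferroni correction procedure will be used to control for multiple comparisons". It states neither the number of comparisons nor whether success needs one or all of them.
- **Estimation of sample size** works from a between-arm difference in the beta T2−T0 change of d = 0.8 ("0.13 mean change or 0.8 SD"), "with a power of 0.80 and an alpha level set at 0.05", and concludes that "a final sample of 21 patients per group has been set for our study".

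**The concern.** Bonferroni named without qualification is normally read as testing each of k comparisons at 0.05/k, whatever happens to the others. Holm's procedure uses the same t tests, also needs no assumption about dependence, keeps the same familywise bound, rejects everything Bonferroni rejects and sometimes more. The article gives no reason for preferring the less powerful of the two.

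With 42 patients this has some weight. The trial is sized on one named comparison, the beta change from T0 to T2, and that comparison shares its alpha with the VR evaluation and possibly with the beta at T3. The VR evaluation uses the same paradigm as the experimental training, so a sizeable VR effect is plausible. In that case Holm would reject the VR null first and then test the beta at a less strict level, with no extra patients.

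**Working it through.** **Inputs.** From the article: 21 per arm, d = 0.8 on the beta T2−T0 change, two-tailed tests, alpha 0.05. Family size is k = 3 (VR T2−T0, beta T2−T0, beta T3−T0), or k = 2 if T3 is kept apart, taking the VR evaluation as one score. The article gives no effect size for the VR evaluation or for the beta at T3, and no correlations between changes. These are assumptions: correlation 0.3 between VR and beta and 0.5 between the two beta changes, with a common correlation of 0 to 0.8 as the range. No dropout is assumed.

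**Step 1: the plan's own figure.** The noncentrality is 0.8 × √(21/2) = 2.59 on 40 degrees of freedom. The exact two-sided t test at 0.05 then has power 0.716, not 0.80; 80% needs 26 per arm. The stated 21 per arm reproduces only as a one-sided test at 0.05. With the correction:

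| Per-test alpha | Power at 21 per arm | n per arm for 80% |
|---|---|---|
| 0.05 (uncorrected) | 0.716 | 26 |
| 0.05/2 = 0.025 | 0.606 | 31 |
| 0.05/3 = 0.0167 | 0.542 | 35 |

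**Step 2: the two procedures.** Bonferroni rejects each null with p ≤ 0.05/k. Holm orders the p values and rejects the i-th smallest while p ≤ 0.05/(k − i + 1), stopping at the first failure. Two things follow.

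- Holm's first step is the Bonferroni test of the smallest p value, so the probability of at least one rejection is the same under both.
- Under Holm the beta test can never face a level looser than 0.05, so its power cannot exceed 0.716. The gain is therefore capped at 0.716 − 0.606 = 0.110 for k = 2 and 0.716 − 0.542 = 0.174 for k = 3. It is collected only when other nulls are also rejected.

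**Step 3: simulation.** Multivariate normal changes, 21 per arm, Student t tests, at least 100,000 trials per scenario, correlations 0.3 and 0.5. Power for the beta T2−T0 test, whose own effect is d = 0.8 throughout:

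| Other primary effects | k | Bonferroni | Holm |
|---|---|---|---|
| All d = 0.8 | 3 | 54% | 63% |
| VR d = 1.2, beta T3 d = 0.8 | 3 | 54% | 66% |
| VR d = 1.2, beta T3 null | 3 | 54% | 60% |
| Both d = 0.4 | 3 | 54.3% | 55.6% |
| Both null | 3 | 54.3% | 54.4% |
| VR d = 0.8 | 2 | 61% | 67% |
| VR d = 1.2 | 2 | 61% | 71% |
| VR d = 0.4 | 2 | 60.6% | 62.0% |
| VR null | 2 | 60.6% | 60.8% |

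With all effects at 0.8, the chance of at least one rejection is about 82% for k = 3 and 80% for k = 2, the same for both procedures. The chance of rejecting all three rises from 25% to 43%, although the article does not make that a success criterion. Over common correlations of 0 to 0.8, Holm's per-test power is 0.61 to 0.63 for k = 3 and 0.65 to 0.67 for k = 2.

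**Step 4: false positives.** With every null true, the familywise error is identical for the two procedures, between 3.6% and 5.0% across the settings. With one real and one null effect (k = 2, correlation 0), the null is rejected in 2.5% of trials under Bonferroni and 4.0% under Holm. Holm uses more of the 5% bound but stays within it.

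**The case against.** The strongest reply is that nothing here is wrong. Bonferroni is a valid, pre-specified correction, nothing in the article conflicts with it, and it brings simple matching confidence intervals, which is a legitimate reason to keep it. The article does not say single-step either, and a step-down implementation could be set out in an analysis plan that is not shown. The first part stands: this is a choice between valid methods, not an error. On the second, plain Bonferroni remains the natural reading, and if a step-down version is intended the sentence should name it.

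A reader might infer three stronger claims that the documents do not support.

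- *That the trial gives away power on its primary outcome without qualification.* The chance of at least one primary rejection does not change, and the gain for the beta nearly vanishes if it is the only real effect. The larger gains need d = 0.8 or more on at least one other measure, for which the article gives no effect size.
- *That the correction is the main reason the beta test may miss.* The uncorrected miss probability is already 1 − 0.716 = 0.284. With three tests it is 1 − 0.542 = 0.458 and with two 1 − 0.606 = 0.394, so 0.284/0.458 = 62% or 0.284/0.394 = 72% of it is present without any correction.
- *That Holm adds no false positives.* It keeps the same 5% familywise bound, but when some nulls are false it uses more of that bound.

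**Conclusion.** The point holds as an optional improvement. For the same 5% familywise bound Holm is never worse than Bonferroni in power. For the comparison the trial is sized on, it adds about 8 to 9 points (three tests) or 6 points (two tests) if all primary effects are d = 0.8, more if the VR effect is larger, about 1 point if the others are d = 0.4, and 0.1 to 0.2 points if they are null. These figures rest on 21 analysed patients per arm, a single VR score and the assumed correlations, to which they are not very sensitive.

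Holm does not bring the design to its stated 80%. It also settles neither the undefined family size nor the use of an unadjusted, two-tailed alpha of 0.05 in a sample size that reproduces only one-sided. Those are separate matters.

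**What to change.** In Statistical methods, replace the reference to a Bonferroni correction by *the Holm step-down Bonferroni procedure (familywise two-sided alpha 0.05)* for the primary tests. Report Holm-adjusted p values beside each between-group difference and its confidence interval. Make the change before any unblinded analysis.

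The cost is one sentence, with no added patients or data. The downside is that Holm has no simple matching simultaneous intervals: intervals given unadjusted or at the Bonferroni level may not always agree with the Holm decision, and the plan should say which are reported. If exact agreement between intervals and tests matters more to the sponsor, keeping Bonferroni with that reason stated is defensible.

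### The secondary analysis defines a T0–T2 change that CBCL and TACQOL cannot have, and uses an unadjusted omnibus MANOVA for domain-specific questions, with instrument age ranges that stop short of age 25

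*Protocol article*

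**What the plan says.** In the protocol article, Statistical methods, the rule for deriving outcomes covers all of them: "For each outcome measure, we calculate the change between T0 and T2", and likewise from T0 to T3. Differences are arithmetic. For the secondary outcomes the method is: "Multivariate analysis of variance will be used to explore differential effects of the trainings in the secondary outcome measures". The same section rules out imputation and states that age and FSIQ, the stratification factors, stay out of the analyses.

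On timing, the Questionnaires section says: "At the baseline (T0) and follow-up evaluations (T3) the TACQOL is administered to parents and children". It continues: "At the same time points, parents are asked to compile the CBCL". The Design section describes the end-of-training visit as one at which "all participants are re-evaluated with the same neurocognitive tests, the VR evaluation scenario and the Action Prediction task". No questionnaire of behaviour or quality of life is listed there. Outcome measures lists both CBCL and TACQOL as secondary outcomes.

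On age, Participants admits patients from 7 to 25 years. Neuropsychological assessment describes NEPSY-II as designed for use "in children and adolescents aged 3–16 years". Outcome measures names the 6–18 form of the CBCL.

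On hypotheses, the Aim section expects gains in social prediction, in implicit learning, in named cognitive domains (attention and executive functions, memory, visuospatial abilities, sensorimotor integration) and in quality of life.

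**The concern.** Three things do not fit together.

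- **A change that cannot be computed.** The derivation rule asks for a T0–T2 difference in two instruments that are not given at T2. TACQOL is the only quality-of-life measure, and quality of life is one of the four listed hypotheses.
- **A method that does not match the question.** The Aim section asks which domains improve. A MANOVA tests whether any linear combination of the included variables differs between groups. By itself it gives no estimate for a domain. It uses complete cases only, so one missing subtest removes the patient from every outcome in that model. Run on change scores without covariates, it also leaves out the T0 value and the two factors on which randomisation was stratified.
- **Instruments that stop before the recruited ages do.** Age-normed scores would not cover patients above 16 (NEPSY-II) or above 18 (CBCL). Raw scores exist for anyone tested, but over a 7–25 age span they vary with age, and the plan excludes age from the model.

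At stake are the interpretability and precision of the secondary results, in a trial of 42 patients. The primary analysis is not affected.

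**Working it through.** **1. Schedule against derivation rule**

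| Secondary outcome | T0 | T2 | T3 | T0–T2 change | T0–T3 change |
|---|---|---|---|---|---|
| NEPSY-II subtests | yes | yes | yes | exists | exists |
| Action Prediction, familiarisation phase | yes | yes | yes | exists | exists |
| CBCL | yes | no | yes | **does not exist** | exists |
| TACQOL (self, parent) | yes | no | yes | **does not exist** | exists |

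**2. Ages.** Trial 7–25; NEPSY-II 3–16; CBCL form 6–18. Neither instrument's range reaches the upper trial age. The article gives neither the age mix nor whether scores are raw or normed.

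**3. The plan's own figure.** No power is stated for the secondary outcomes. The only figure is for the primary: 21 per group, d = 0.8, two-tailed, alpha 0.05, power 0.80. With 21 per group the noncentrality is (21 × 21 / 42) × 0.8² = 10.5 × 0.64 = 6.72. On F(1, 40), critical value 4.085, this gives power 0.72, not 0.80. That gap is a separate matter; 0.72 is used here only as the single-outcome benchmark.

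**4. MANOVA power (two-group Hotelling T²).** F with p and N − p − 1 degrees of freedom; noncentrality λ = (n₁n₂/N) · δ′Σ⁻¹δ.

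- Number of variables, p = 10, counted from Outcome measures: Theory of Mind, emotion recognition, familiarisation accuracy, familiarisation reaction time, Inhibition, Visual Attention, two puzzles, Memory, Finger-tapping.
- N = 42, so the degrees of freedom are 10 and 31 and the critical F is 2.153.
- Assumed, not in the documents: equal correlation r between outcomes, from 0 to 0.5; d = 0.8 on each affected measure.

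With one affected measure, δ′Σ⁻¹δ = 0.64 × [1 + 8r] / [(1 − r)(1 + 9r)]:

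- r = 0: λ = 10.5 × 0.64 = 6.72, power 0.28
- r = 0.3: λ = 10.5 × 0.64 × 3.4/2.59 = 8.82, power 0.37
- r = 0.5: λ = 10.5 × 0.64 × 5/2.75 = 12.22, power 0.51

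| Measures affected (of 10), d = 0.8 | r = 0 | r = 0.3 | r = 0.5 |
|---|---|---|---|
| 1 | 0.28 | 0.37 | 0.51 |
| 2 | 0.56 | 0.65 | 0.81 |
| 3 | 0.77 | 0.81 | 0.93 |
| all 10 equally | >0.99 | 0.72 | 0.51 |

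At d = 0.5 with one measure affected, power is 0.12 to 0.20. For comparison, one unadjusted t test on the affected outcome has power 0.72 (d = 0.8) or 0.35 (d = 0.5). At the Bonferroni level over 10 outcomes these fall to 0.37 and 0.10.

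**5. What adjustment for baseline adds.** Let ρ be the T0–post correlation and take equal variances σ² at both visits. The residual variance is 2σ²(1 − ρ) for a change score and σ²(1 − ρ²) for ANCOVA, a ratio of (1 + ρ)/2. This is below 1 for any ρ < 1. For an assumed ρ of 0.5 to 0.8 it is 0.75 to 0.90. The cost is small: intercept, group, T0 value, one age-stratum term and two FSIQ terms use 6 degrees of freedom and leave 42 − 6 = 36.

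**The case against.** The strongest reply is that the sentence on MANOVA only undertakes to explore. It fixes no visit, no list of variables and no single model. A T0–T2 MANOVA on NEPSY-II and the familiarisation measures is computable, and at T3 every secondary measure is scheduled. Univariate follow-up after an omnibus test is routine and may be in an analysis plan that is not shown. No power is claimed for these outcomes. This much stands, and it rules out three stronger readings that a reader might infer.

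- **That the MANOVA cannot run.** Only the T0–T2 change for CBCL and TACQOL is impossible. The remaining models can be fitted.
- **That older patients would be lost wholesale.** This would follow only if normed scores were used and none existed above the stated ages. The article does not say that scores are normed; the battery is given to all participants, and raw differences exist for everyone tested.
- **That there is almost no power.** This needs the least favourable case. One T3 model with 10 measures, 3 CBCL dimensions and 7 × 2 TACQOL scales (27 variables, or 28 with delayed memory recall) would have power 0.11 to 0.17 for one affected measure at d = 0.8, but the article specifies no such model. With 10 variables the range is 0.28 to 0.51, and two or three responding measures raise it to 0.56–0.93. Separate tests with a Bonferroni correction over 10 would reach only 0.37, so power alone does not decide against MANOVA.

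What the reply does not answer is the derivation rule that contradicts the article's own schedule, the stated exclusion of age and FSIQ from the analyses, and the mismatch between an omnibus test and hypotheses about separate domains. These are written in the article; they are not details left out.

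**Conclusion.** The point holds as a fault in the stated analysis that should be corrected. The contradiction over CBCL and TACQOL is certain on the text; the study-design figure was not available to check. The age mismatch is also certain as a mismatch. Its consequence depends on the scoring: normed scores would leave older patients uncovered, while raw scores cost precision unless age is modelled. Randomisation protects the group comparison from bias in either case.

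The case against MANOVA rests on fit and precision: no domain-level estimate, complete cases across all included variables, and no use of T0 values or strata. It assumes that the MANOVA is run on the change scores, the natural reading of the section. The power figures (0.28 to 0.51 for one affected measure of 10) rest on assumed effect sizes and correlations and serve only to show scale.

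**What to change.** Replace the MANOVA sentence and limit the derivation rule to visits that exist:

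- For each secondary outcome, fit an ANCOVA of the post-training value on group, the T0 value, and the age and FSIQ strata, using every patient who has that outcome. Report the adjusted difference with its 95% CI and label the set exploratory.
- Analyse CBCL and TACQOL at T3 only. Analyse NEPSY-II and the familiarisation measures at T2 and at T3.
- Use NEPSY-II raw scores with age in the model. Age in years is preferable there, because the upper stratum runs from 13 to 25.
- Limit the CBCL analysis to patients within the form's age range, and report how many that is.

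The cost is wording only: no new data, visits or patients. The downside is more results to report. The exploratory label handles this and avoids the power lost to a correction over many outcomes. The CBCL analysis will rest on fewer patients than the others, by a number that the article does not allow one to predict.
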